### Blinding

It is impossible for a supervised intervention study to be double-blind, only the investigators who performed the assessment and MRI scanning are blinded to group assignment. In further, participants are blinded to the specific hypothesis of the study. To reach proper blinding, we have selected real and sham coils that are similar in shape, size, color, and weight, and that emit extremely similar sounds. The participants, their relatives and the evaluating neuropsychologist will be blinded to group allocation and the timing of the intervention will be set at different times in order to minimize the loss of blinding. All assessments will be conducted through a blinded database deliciated through “A” or “B” labels. Participants will be grouped by investigators not involved in the intervention. Moreover, participants will be unblinded participants when any clinical situation associated with adverse events or patient withdrawal occurs.

### Interventions

Subjects will be screened according to their demographic information and medical history. Upon confirmation of participant eligibility following baseline assessments, participants will be randomly allocated to sham rTMS groups, real rTMS groups, and cognitive training groups in a 1:1:1 ratio. A total of four neuropsychological assessments will be performed: at baseline (T1), after the 10th rTMS session (T2), after the 20th rTMS session (T3), and 30 days following rTMS (T4).

### rTMS

rTMS with a focal figure-of-8-shaped coil (i.e., active and sham coils) will be performed among all participants. The sham coil has the same size and shape as the active coil. However, it does not create any significant magnetic field.

The coils of the transcranial magnetic stimulator will be placed on the patient's left and right dorsolateral prefrontal cortices (DLPFC) based on the F3 and F4 positioning specified in the International 10–20 system for conducting electroencephalography (EEG) (24). The stimulation intensity will be set at a 100% threshold by measuring the threshold of the hallux abductor muscle. rTMS will be delivered to the left DLPFC at a frequency of 10 Hz (5 s durations, 25 s pauses) for a total of 2,000 pulses (50 pulses per train, 40 trains). rTMS will likewise be delivered to the right DLPFC at a frequency of 1 Hz (5 s durations, 25 s pauses) for a total of 2,000 pulses (40 pulses per train, 50 trains). There will be a total of 20 intervention sessions.

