Recently, repetitive transcranial magnetic stimulation (rTMS), a neuromodulatory tool, can induce neural activity and efficiently improve cognitive function (12–15). A large number of existing studies confirm that repetitive transcranial magnetic stimulation (rTMS) of the dorsolateral prefrontal cortices (DLPFC) may strengthen the connections within the brain network, which may increase the strength of the interconnections between the cortex and hippocampus, resulting in cognitive enhancement (16, 17). High frequency (≥ 5) rTMS (HF-rTMS) is the most widely used technique to improve cognitive function in clinical trials as well as in healthy individuals (18). In a review of cognitive enhancemen using rTMS, 10 Hz was found to be the frequency used in most studies (19). Most studies found that HF-rTMS on left DLPFC improved memory and processing skills in healthy, depressed, posttraumatic stress disorder (PTSD), schizophrenic, AD, and mild cognitive impairment (MCI) populations. However, some showed no significant effect. In another review of the efficacy of LF-rTMS on cognition, the findings of 1 Hz rTMS on the right DLPFC on improving cognitive function in mood disorders, psychosis, stroke and other organic disorders were also inconsistent (20).

A Systematic Review Also Reported That RTMS Enhances Neuroprotection and Recovery Following TBI in Animals (21). However, There Have Been Fewer Studies Investigating the Effects of RTMS on Cognitive Function in Humans Presenting With TBI, and Most Investigations to Date Have Been Clinical Case Reports or Case Series. To the Best of Our Knowledge, Only two RCTs Have Been Reported to Dates Neville et al. Reported That Stimulating the Left DLPFC With 10 Hz RTMS Did not Improve Cognitive Function in Subjects, While Lee and Kim Stimulated the Right DLPFC With 1 Hz RTMS, Which Improved Cognitive Function in Subjects (22, 23). They Reported the Safety and Efficacy of Implementing RTMS on Bilateral DLPFC and may be an Alternative Type of Intervention to Improve Cognitive Function. Also, Some Studies Suggested That at Least 4 Weeks of RTMS Intervention may be Necessary to Improve Cognitive Function.

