Therefore, the proposed study aims to examine HF and LF, bilateral rTMS for the cognitive dysfunction in patients with TBI. In addition, magnetic resonance imaging (MRI) will be utilized to explore the association between brain structure and functional connectivity, as well as the cognitive effects of rTMS. The preliminary hypotheses of our study are (1) 4 weeks of bilateral high- and low-frequency rTMS is more effective in improving cognitive function in patients with TBI than sham stimulation and cognitive training and (2) structure MRI markers and functional connectivity pre- and post-intervention will be observed.

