## Materials and Methods

### Study Design

The study is a prospective randomized placebo controlled, parallel-group trial that will be conducted at the Affiliated Hospital and the Second Clinical Medical College of North Sichuan Medical University. The protocol has been registered with the China Clinical Trial Registry (item number: ChiCTR2100050753). Our study will show improvement in cognitive function in patients with TBI following rTMS bilateral DLPFC intervention. The findings may provide a rationale for an approach of rTMS intervention for cognitive function in patients with TBI. Thirty-six patients with TBI will be enrolled in the trial. The physicians will provide patients with detailed information about the trial in verbal and written form before the trial begins.All patients will voluntarily sign an informed consent form. All patients will be screened according to eligibility criteria. 36 subjects will be randomized in a 1:1:1 ratio into the real-rTMS group, the Cognitive training group and the sham-rTMS group. All subjects will be required to perform neuropsychological assessments at before intervention, post-10 sessions, post-20 sessions, and 30 days after the intervention. MRI will be performed at pre-intervention and post-20 sessions. All patients will receive intervention for 4 weeks (30 minutes per day, 5 days per week). The diagram and schedule for the study are shown in Figure 1 and Table 1.

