In our study, we will apply rTMS on bilateral DLPFC, which differs from the previous intervention protocols. It has likewise been reported that rTMS applied to both the left and right DLPFC can be administered in the effective treatment of depression and can improve serum neuron-specific enolase (NSE) and brain-derived neurotrophic factor (BDNF) levels as well as temporal perception in neurologic patients, causing an overall protective effect on neurological function (34, 37, 38). It has been pointed out that HF-rTMS can significantly improve executive function in patients with cerebrovascular disease, and LF-rTMS can improve attention deficit or inattention in patients with depression and schizophrenia (39). In addition to executive function and memory loss, depressed or dryness are also common symptoms in TBI patients, and these long-term mood disorders can also indirectly contribute to cognitive behavior (1). We performed bilateral rTMS on subjects simultaneously, which may improve both the cognitive difficulties driven by neurological injury and the individual's mental status, thus effectively improving the cognitive abilities of TBI patients.

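### The right-side 1 Hz settings contradict each other: 5 s trains give 250 pulses, not 2,000, and 2,000 pulses at 1 Hz do not fit in 30 minutes

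*Protocol article*

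**What the plan says.** The rTMS section of the protocol article gives the two sides in parallel sentences.

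- Left DLPFC: "10 Hz (5 s durations, 25 s pauses) for a total of 2,000 pulses (50 pulses per train, 40 trains".
- Right DLPFC: "1 Hz (5 s durations, 25 s pauses) for a total of 2,000 pulses (40 pulses per train, 50 trains".

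The section then states: "There will be a total of 20 intervention sessions". It gives no rTMS session length and does not say whether the two sides are treated in turn or together.

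Other places bear on these settings:

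- Study Design: "All patients will receive intervention for 4 weeks (30 minutes per day, 5 days per week".
- Introduction, on what counts as high frequency: "High frequency (≥ 5) rTMS (HF-rTMS) is the most widely used technique".
- Introduction, first hypothesis: "4 weeks of bilateral high- and low-frequency rTMS is more effective in improving cognitive function in patients with TBI".
- Discussion: "We performed bilateral rTMS on subjects simultaneously".

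The Abstract also assigns 10 Hz to the left side and 1 Hz to the right.

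**The concern.** Frequency, train duration and pulses per train are tied together: any two fix the third. The right-side sentence states all three, and they disagree. The left-side sentence has the same layout and agrees exactly, so the layout is not the cause.

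An operator cannot program the right side from the printed text, and the possible repairs give different treatments. One cuts the right-side dose to an eighth. Another keeps the dose but takes the session past the stated daily time. A third turns the low-frequency side into what the Introduction classes as high frequency, which would undercut a hypothesis about combined high- and low-frequency stimulation. The protocol lists seizures among the possible adverse events, which is a further reason for the delivered settings to be unambiguous.

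Daily time matters for the comparison as well. Cognitive training is fixed at 30 min per session, so a longer rTMS session would end the equal daily time that Study Design states for all patients.

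**Working it through.** **Inputs.** From the rTMS section:

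- Left: 10 Hz, 5 s on, 25 s off, 50 pulses per train, 40 trains, 2,000 pulses.
- Right: 1 Hz, 5 s on, 25 s off, 40 pulses per train, 50 trains, 2,000 pulses.
- Sessions: 20.

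From Study Design: 30 min per day.

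**Formulas.**

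- Pulses per train = frequency × train duration.
- Total pulses = pulses per train × trains.
- Time = trains × (train duration + pause).

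**Left side.** 10 × 5 = 50 pulses per train; 50 × 40 = 2,000 pulses; 40 × 30 s = 1,200 s = 20 min. The plan's figures are reproduced.

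**Right side.** The plan's own product is correct: 40 × 50 = 2,000. The 40 is not reproduced: 1 × 5 = 5 pulses per train, and 5 × 50 = 250 pulses.

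**What each repair implies.**

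| Kept | Given up | Frequency | Pulses | Right-side time |
|---|---|---|---|---|
| 1 Hz, 5 s/25 s, 50 trains | 40 per train; 2,000 total | 1 Hz | 250 | 50 × 30 s = 25 min |
| 1 Hz, 40 per train, 50 trains, 25 s pause | 5 s trains (become 40 s) | 1 Hz | 2,000 | 50 × 65 s = 3,250 s = 54.2 min (53.75 min without the last pause) |
| 1 Hz, 2,000 total, no pauses | 5 s trains; 25 s pauses | 1 Hz | 2,000 | 2,000 s = 33.3 min |
| 5 s/25 s, 40 per train, 50 trains | 1 Hz | 40/5 = 8 Hz | 2,000 | 25 min |
| 1 Hz, 5 s/25 s, 2,000 total | 40 per train; 50 trains (become 2,000/5 = 400) | 1 Hz | 2,000 | 400 × 30 s = 200 min |

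**Against the 30 min session.** At 1 Hz, 30 min holds 30 × 60 = 1,800 pulses at most. Every row that keeps both 1 Hz and 2,000 pulses exceeds 30 min on the right side alone, so treating the two sides at the same time does not help.

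The 250-pulse row takes 25 min and fits if the sides run together. If they ran in turn, the left side would add 20 min: 25 + 20 = 45 min for 250 pulses, and 33.3 + 20 = 53.3 min to 54.2 + 20 = 74.2 min for 2,000 pulses without pauses or with 40 s trains and 25 s pauses.

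**Size.**

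- Right side per session: 2,000/250 = 8-fold.
- Right side over 20 sessions: 250 × 20 = 5,000 against 2,000 × 20 = 40,000.
- Both sides per session: 2,000 + 250 = 2,250 against 4,000, a ratio of 1.78.
- Both sides over 20 sessions: 45,000 against 80,000.

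**The case against.** The strongest reply is that the readings are not equally likely. Four right-side figures agree with one another: 1 Hz, 40 per train, 50 trains and 2,000 in total. Only the 5 s duration conflicts with them, and the bracket that holds it is identical to the left-side one, so a carry-over is the simplest explanation. On that view 250 pulses is an outer bound, since it discards two stated figures to save one. The 8 Hz reading conflicts with the Abstract, the hypothesis and the sentence itself, and the 200 min reading conflicts with the stated train count. This is fair as a ranking, and the intended frequency is hardly in doubt. But a carry-over is an inference: nothing in the article gives another 1 Hz train duration, so the correct value still has to come from the sponsor.

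The 30-minute point can also be pressed. It takes 2,000 as a per-session figure, which the text does not say outright. It also treats an all-arm summary as a ceiling on stimulation time, and without pauses the excess is only 33.3 against 30 min, about 11%. The per-session reading is nevertheless the only workable one, since 50 trains spread over 20 sessions would be 2.5 trains a session. And if the carry-over explanation is accepted with the 25 s pause kept, the excess is about 24 min, well beyond rounding. If the pause is suspect too, that is one more setting to correct.

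The in-turn times run against the Discussion, which describes the two sides as simultaneous. They are therefore conditional, and neither conflict depends on them.

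Finally, no sample size or analysis figure rests on this, and the comparison of real with sham is not biased if both coils follow one schedule. That is correct and limits the harm to dose definition, reproducibility and session length.

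**Conclusion.** The concern holds. The conflict between 1 Hz, 5 s and 40 pulses per train follows from the printed figures alone, whether the 2,000 pulses are per session or per course. Its outer size is eightfold on the right side (250 against 2,000 pulses).

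The conflict with session length holds on the assumption that 2,000 is per session: at least 33.3 min, and about 54 min with 40-pulse trains and the stated pauses, against 30 min.

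The left side is sound. Which right-side figure is wrong cannot be settled from the article. Because the error sits in the definition of the experimental treatment, it must be corrected, even though no statistical result depends on it.

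**What to change.** Check the device program and the ethics-approved protocol. Then replace the right-side sentence in the rTMS section with one consistent 1 Hz set: train duration, pause, pulses per train, number of trains and total, labelled per session. In the same place, say whether the two sides are treated in turn or together, so that the Discussion's description can be checked against it.

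Then compare the resulting time with Study Design. If it exceeds 30 min, correct the stated rTMS session length there. If 30 min is kept, the right side can have no more than 1,800 pulses at 1 Hz, and fewer if there are pauses. Use the same schedule for the real and sham coils.

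The cost is one sentence, possibly a second one on session length, and a check of the settings. The downside is that either the rTMS session becomes longer than the cognitive training session or the stated right-side dose comes down.

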#### Cognitive Training

Subjects will be given computer-assisted cognitive training. The computer system is used for cognitive function training, and patients are guided by professionally trained therapists. The task areas include: (a) visuospatial training; (b) executive function and problem solving; (c) attention training; (d) memory training; and (e) calculation training. There are over 20 different therapeutic tasks for training, and the difficulty of the tasks in each area increases automatically as the participant successfully performs the simpler tasks. The cognitive training schedule was 30 min/session, 1 session/day, 5 days/week, with a treatment period of 4 weeks.

### Dropout Criteria

The intervention will be discontinued if the subject meets one or more of the following criteria (a) Subjects who are enrolled incorrectly; (b) Subjects have poor compliance and do not follow treatment as required, as when subjects fail to cooperate with investigators, or when subjects are unable to remain quiet and immobile, or when subjects do not come to treatment on time; (c) Inadequate medical record that interferes with efficacy or safety evaluation; (d) Subjects drop out voluntarily; (e) The subject develops adverse events (including seizures, pain, irritability, etc.); (f) There is severe progression of the subject's condition or some comorbidities, complications, or specific physiological changes; and (g) The subject is considered by the investigator to be unsuitable for further participation in this study.

### Screening Assessment

#### Rancho Los Amigos Scale of Cognitive Functioning (RLAS)

At present, the severity of cognitive impairment following TBI is considered a spectrum that ranges from I to X based on Rancho Los Amigos Scale of Cognitive Functioning (RLAS) scoring. RLAS describes ten states of cognitive and behavioral functioning that patients with brain injury typically progress through. Higher values indicate increased functioning (25).

#### The Chinese Version of Montreal Cognitive Assessment (MoCA)

This assessment scale is comprised of domains measuring attention and concentration, executive functioning, memory, language, visuospatial ability, thinking, calculation, and orientation. The scale consists of eight cognitive domains for which subjects are required to 30 questions. Each correct answer is given 1 score, while incorrect answers or no answers are given 0 score. The cut-off value for the MoCA in the Chinese population is ≥26 (26).

### Outcome Measures

The primary outcome of the proposed study is current executive functioning as measured by the Shape Trail Test (STT), which was revised for the Chinese-speaking population based on the Trail Making Test (TMT). The secondary outcome measures are neuropsychological test findings based on the Hopkins Verbal Learning Test (HVLT), the Brief Visuospatial Memory Test (BVMT), and the Digit Span Test (DST), as well as evaluations of the safety and tolerability of rTMS in patients with TBI.

### Neuropsychological Tests

#### STT

The STT comprises a series of Arabic numerals combined based on Chinese cultural competency and consisting of two parts (27). Part A consists of 25 digits. The participants are asked to connect the numbers as instructed prior to the test. Part B likewise contains 25 digits. However, each digit appears twice (in a circle and in a square). The digits need to be alternately connected by the participants as pre-instructed. The time required for the subject to complete the task will be recorded, less time suggesting better executive function. The test shows an acceptable level with respect to area under the curve (AUC = 0.835), sensitivity (84.6%), and specificity (66.7%) values among elderly people (> 65 years) with an education level <12 years (26).

#### HVLT

This tool assesses memory impairment during vocabulary learning, including evaluations of immediate and delayed memory (28, 29). The test consists of 12 words (three categories, four words per category). Once the words are removed following each display, the participants are immediately asked to recall as many words as they can. There is no requirement for order of recall and there is no time limit for this test. The number of correct words is recorded to calculate the total score. The procedure will be repeated three times for a total score range of 0–36. The test is structured such that a higher score delineates a better memory.

#### BVMT

This test is used to measure visuospatial memory (30). In this test, the examiner presents the participant with a scale consisting of six geometric figures for a total of 10 s each. The participant is then asked to draw as many figures as possible in the correct order. The test is repeated three times. Each figure drawn by the subject was scored according to the criteria provided in the test booklet. Two points are awarded for each figure if it is accurately reproduced and correctly located. Those that are properly placed or drawn correctly receive 1 point. Those with blank answer sheets or no identifiable picture found receive 0 points. The possible scores for a single test range from 0 to 12. The total score is the sum of the scores from the three trials. The test is structured such that a higher score delineates a better memory.

#### DST

The digit span test consists of a forward number test and a backward number test (31). In these two subtests, the examiner reads out a series of numbers to the participant. Participants are asked to repeat the numbers in the same or the opposite order. The digits range from 1 to 9, and the series length is from 2 to 9, for each series length with two trials (e.g., 4–6, 7–5, 2–4–7, 9–6–3, etc.). The test was stopped when the subject missed two trials of a series length. Memory span were scored as the number of items in the longest series recalled forward and backward.

#### Functional Magnetic Resonance Imaging (fMRI) Data Acquisition

Imaging for all participants will be acquired using a Siemens 3.0 T magnetic resonance scanner (Siemens MAGENETOM Trio; Siemens Healthcare, Malvern, PA, USA). The main sequences of the MRI scan and their parameters are as follows. For 3D–T1 weighted imaging, the spoiled Gradient-echo sequence will be selected with the following scan parameters: TR = l,900 ms, TE = 2.48 ms, field of view (FOV) = 250 × 250 mm, layer thickness = 1 mm, layer spacing = 0 mm, matrix = 256 × 256, and flip angle (FA) = 900, with a total of 176 layers. For resting-state fMRI, an echo-planar imaging sequence (EPI) sequence will be selected with the following scan parameters: TR = 2,000 ms, TE = 25 ms, and field of view (FOV) = 240 × 240. The parameters of the FLAIR (fluid-attenuated inversion recovery) sequence are as follows: TR = 8,500 ms, TE = 94 ms, field of view (FOV) = 250 × 250 mm, layer thickness = 0 mm, matrix = 64 × 64, flip angle (FA) = 900, number of layers = 36, total time points acquired = 240 [250 × 250 mm, layer thickness = 5 mm, number of layers = 20, and voxel size = 1.3 × 0.9 × 5 mm^3^]). The scanning time required for each participant is approximately 30 min.

#### Rs-fMRI Data Analysis

Resting-state fMRI images will be preprocessed and regional homogeneity (ReHo) analyses will be performed using DPARSF (Data Processing Assistant for Resting-State fMRI), REST (Resting-State fMRI Data Analysis Toolkit), and SPM8 (Statistical Parametric Mapping) software. Matrix Lab (Matlab2012b; MathWorks, Natick, MA, USA) has been chosen as the platform for data processing. In consideration the time required for participants to adapt to the scanning environment, we will remove the first ten time points from each subject's blood oxygen level dependent (BOLD) sequence; the remaining 230 time points will be subjected to time series corrections, head movement corrections, and head movement parameter tests. If the participants' head movement angle is **>** 2.00 at any angle of x, y, or z or if the maximum translational head movement is **>** 2.0 mm, the participant's data will be rejected. Next, the data space for each participant will be normalized to the Montreal Neurological Institute (MNI) standard space with resampled voxels of 3 × 3 × 3 mm. Six head movement parameters, mean white matter signals, mean whole brain signals, and mean cerebrospinal fluid signals will be removed as covariates and then subjected to de-linearization drift and filtering processing (0.01–0.08 Hz) to eliminate high frequency noise, such as from respiration and heartbeats. Based on the above processed data (i.e., for the ReHo analysis), the ReHo value of each voxel, termed Kendall's coefficient, will be obtained by calculating the consistency of the time series of each voxel and its surrounding adjacent 26 voxels. The ReHo value for each voxel of the whole brain comprises a complete ReHo map. For normalization, the ReHo map of each individual is divided by the average ReHo value of the whole brain. The final obtained image will then be smoothed with full width at half maximum (FWHM) = 4 × 4 × 4 mm. Post-processing of ALFF will likewise be analyzed using REST software. After combining the six cephalomotor parameters, the mean white matter signals, the mean whole brain signals, and the mean cerebrospinal fluid signals will be de-linearized and filtered (0.01–0.08 Hz) before being removed as covariates. After that, the filtered time series will be transformed to the frequency domain range via Fourier transform and a power spectrum at 0.01–0.08 Hz will be calculated. The square root of the power spectrum will be designated as the ALFF value. Each voxel-split ALFF value is divided by the mean value of all voxel ALFFs in order to obtain normalized mean ALFF values. Finally, all covariates will be removed. Functional connectivity analyses will be performed using ALFF with the brain regions of intergroup differences obtained by the ReHo method as seed points in order to assess whole-brain functional connectivity via gray matter templates.

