In the proposed study, resting-state functional magnetic resonance imaging (rs-fMRI) will be used to explore the pathophysiological processes mediating TBI cognitive dysfunction through DLPFC stimulation delivered through rTMS. Disruption of brain network connectivity is an important mechanism leading to cognitive dysfunction in TBI (40); cognitive dysfunction may be primarily associated with disruptions to the default mode network (DMN) (41, 42). The DMN is a task-negative network that is preferentially activated when the individual is not concerned with the external environment and involves several internal cognitions, such as autobiographical memory extraction, looking into the future, envisioning others' perspectives, and processing emotional cognition (43). A recent study found that the DMN is not a single network but rather consists of several intertwined networks. The DMN exhibits positive correlations across internal regions as well as negative correlations with relevant regions of external attentional processing (30). A review of 17 original studies conducted in patients with TBI showed that 53% of these studies reported that rTMS promotes increased brain connectivity, 18% reported that rTMS is associated with decreased functional connectivity, and 29% reported no changes in brain connectivity following rTMS (31). The DLPFC is an important component of the DMN network and its use as a rTMS stimulation site may modulate functional connectivity in the DMN. It is possible that connections within and outside the DMN are transmitted through the paracentral hippocampal cortex and posterior cingulate gyrus as nodes for information transmission (44, 45). As shown by Shang et al. rTMS on the left DLPFC alters the resting-state functional connectivity from the DLPFC to the hippocampal parietal, posterior cingulate cortex (PCC)/precuneus regions in the DMN network (16).

As age, education level, TBI severity, and patients' state of consciousness have been reported as factors influencing patients' cognition (8), this study was proposed to conduct subgroup analyses following measurements of baseline levels of RLAS and MoCA to reduce the effects of raw scores on the obtained results. The rTMS in this study applied to two sites of targeting and may have different efficacy in different subjects, providing a new direction for rTMS intervention in cognition in TBI.

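### Functional connectivity is to be computed from ALFF, which has no time course, and with seeds set only by ReHo group differences the DLPFC-based imaging rationale has no prespecified test

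*Protocol article*

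**What the plan says.** All the analysis steps are in the protocol article, Rs-fMRI Data Analysis.

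- **Time series.** After the first ten volumes are dropped, "the remaining 230 time points will be subjected to time series corrections, head movement corrections, and head movement parameter tests". Motion, white-matter, whole-brain and cerebrospinal-fluid signals are removed as covariates, and the data are filtered to 0.01–0.08 Hz.
- **ALFF.** The filtered series is Fourier-transformed. "The square root of the power spectrum will be designated as the ALFF value". Then "Each voxel-split ALFF value is divided by the mean value of all voxel ALFFs in order to obtain normalized mean ALFF values". The next sentence reads "Finally, all covariates will be removed".
- **Connectivity.** "Functional connectivity analyses will be performed using ALFF with the brain regions of intergroup differences obtained by the ReHo method as seed points", and this is done "in order to assess whole-brain functional connectivity via gray matter templates".

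The imaging rationale is given elsewhere. The Introduction says that DLPFC stimulation "may increase the strength of the interconnections between the cortex and hippocampus, resulting in cognitive enhancement". The Discussion says "The DLPFC is an important component of the DMN network and its use as a rTMS stimulation site may modulate functional connectivity in the DMN", and cites a study in which left-DLPFC stimulation altered DLPFC connectivity with hippocampal and posterior cingulate/precuneus regions. The rTMS section fixes the stimulation sites at F3 and F4. No section names the DLPFC, a default mode node or the hippocampus as a seed.

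Table 1 places brain connectivity by fMRI in the secondary-outcome block. The Abstract and the Outcome Measures section list the secondary outcomes without it.

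**The concern.** There are two separate problems.

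First, the named input does not fit the named analysis. A seed-to-voxel connectivity value is the correlation over time between the seed's signal and another voxel's signal within one scan. ALFF, as the article defines it, has discarded the time axis and the phase. An analyst who followed the text literally could not produce the outcome, and a reader could not reproduce it.

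Second, the seed rule does not lead to the question that the rationale raises. ReHo measures how far a voxel agrees with its 26 immediate neighbours. Long-range connectivity of the DLPFC could change with no local ReHo difference there, and the DLPFC would then never become a seed.

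At stake are the connectivity entry in Table 1, the functional-connectivity part of hypothesis 2, and the planned correlations between change in MRI measures and change in behavioural measures.

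**Working it through.** The article gives no numerical figure on this point to reproduce. Two checks were made.

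**1. Can connectivity be derived from ALFF?**

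Inputs: 240 volumes minus 10 dropped = 230 time points; TR 2 s; band 0.01–0.08 Hz (fMRI data acquisition and Rs-fMRI Data Analysis sections).

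Write two band-limited series with Fourier amplitudes *a*ₖ and *b*ₖ and phase differences Δₖ. Then

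- ALFF of the first series depends on the *a*ₖ only, and ALFF of the second on the *b*ₖ only;
- *r* = Σ *a*ₖ*b*ₖ cos Δₖ / √(Σ*a*ₖ² · Σ*b*ₖ²).

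With equal amplitudes this reduces to *r* = Σ *a*ₖ² cos Δₖ / Σ *a*ₖ². The correlation is then set by the phases, which ALFF does not contain. A simulation with these settings (32 frequency bins in the band, arbitrary signal units) gave:

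| Phase relation | ALFF, series 1 | ALFF, series 2 | *r* |
|---|---|---|---|
| Same | 0.0932 | 0.0932 | +1.00 |
| Quarter cycle | 0.0932 | 0.0932 | 0.00 |
| Random | 0.0932 | 0.0932 | -0.36 |
| Opposite | 0.0932 | 0.0932 | -1.00 |

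Identical ALFF values are compatible with perfect positive, absent and perfect negative connectivity. Dividing by the mean over voxels only rescales ALFF and restores nothing.

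**2. How likely is a given region, such as the DLPFC, to become a seed?**

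Inputs: independent *t*-tests at P < 0.001 (Statistical Analysis); 12 per arm, or 10 after the dropout allowance (Sample Size Estimation). Assumptions: a two-sided test, one comparison of two arms, and the true standardised ReHo difference *d*, which the article does not give. The value 0.7 is borrowed from its cognitive effect size; 1.0 and 1.5 show the range.

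Power is from the noncentral *t* distribution with 2*n* − 2 degrees of freedom and noncentrality *d*√(*n*/2). For *d* = 0.7 the noncentrality is 0.7 × √5 = 1.57 at *n* = 10 and 0.7 × √6 = 1.71 at *n* = 12.

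| *d* | *n* = 10 per arm | *n* = 12 per arm |
|---|---|---|
| 0.7 | 2.6% | 3.8% |
| 1.0 | 8.5% | 12.9% |
| 1.5 | 33.5% | 47.5% |

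Under moderate differences a DLPFC seed is possible but unlikely. These figures are for one prespecified region. They are not the chance that no seed appears anywhere in the brain.

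**The case against.** The strongest reply has four parts.

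- **The ALFF wording is probably a slip.** The pipeline already yields the right input, the nuisance-regressed and filtered BOLD series. Since the literal instruction cannot be carried out, an analyst would notice and use that series. This is plausible, and it means that silent bias is not the main risk. The stated method is still wrong and needs correcting; this is not detail left to a fuller document.
- **The mechanism is not left wholly unexamined.** A reader might infer that the DLPFC link goes untested. The documents do not support that. The map covers the whole brain, so a ReHo seed in the DLPFC, or one in a default mode or hippocampal region with the DLPFC as target, would examine it. What stands is that no such test is prespecified.
- **There is no formal DLPFC hypothesis.** Hypothesis 2 names no region, and the Discussion presents the imaging as exploratory and the mechanism as a possibility. Data-driven seeds are a legitimate choice for an exploratory aim, and a condensed article may leave seed coordinates elsewhere. This limits the weight of the point. However, the article does not simply omit the seeds: it gives a rule for them, and that rule does not guarantee an answer to the question motivating the scans.
- **The final covariate sentence is ambiguous.** A reader might infer that time-series nuisance signals are to be regressed from single ALFF values, which would be impossible. The sentence names no covariates. It may repeat the earlier step or mean subject-level covariates, so only a request for clarification is warranted.

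Nor should one infer that there will probably be no seed at all. No cluster rule or multiplicity correction is stated. With an assumed 40,000 to 70,000 voxels, 40,000 × 0.001 = 40 to 70,000 × 0.001 = 70 would pass by chance alone.

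**Conclusion.** The point holds in two parts. The connectivity method is described wrongly: as the article defines ALFF, within-scan seed-based connectivity cannot be derived from it. This follows from the definition and rests on no numerical assumption. The seed rule also leaves the DLPFC-to-default-mode and hippocampal rationale without a prespecified test. The chance that a given region becomes a seed is roughly 3% to 4% at a standardised difference of 0.7, rising to 34% to 48% at 1.5; these percentages depend on the assumed difference and a two-sided test.

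The consequence is limited. Connectivity is a secondary or exploratory outcome whose status is itself uneven across Table 1, the Abstract and Outcome Measures. The primary outcome, the Shape Trail Test, is not affected. The change should be made, but the trial does not depend on it.

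**What to change.** 1. State that functional connectivity is computed from the nuisance-regressed, 0.01–0.08 Hz filtered, 230-point BOLD time series, and remove the reference to ALFF as its input.
2. Prespecify the left and right DLPFC regions under F3 and F4 as seeds, and keep the ReHo-derived seeds as exploratory.
3. Say which covariates the last sentence of the ALFF description refers to, or delete it if it repeats the earlier nuisance regression.

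The cost is some rewording, two predefined regions and a small amount of extra analysis on the same scans. No added patients, visits or scans are needed.
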